### Withdrawal of consent

Participants will be informed that taking part is completely voluntary and that they are free to withdraw from the study at any time without prejudice and without having to give a reason. They may also be removed at any time from the study if adverse events or any exclusion criteria are detected. If a disease is discovered during the study, subjects will be offered a medical follow-up adapted to it. Withdrawals of consent will be replaced.

### Data management and statistical analyses

All collected information will be registered in physical files (case report files (CRFs)), previously anonymised with the participant’s randomisation code in order to respect confidentiality at all times. Computer test data (BART, EEfRT) and physical test results will be collected in electronic format.

All researchers and trained staff called upon to collaborate in the tests are bound to secrecy.

Analyses will be performed using the SAS® 9.4 Software for Windows (SAS Institute©, Cary, NC, USA). Categorical variables will be described in terms of effective, absolute, and relative frequencies for each modality. Continuous variables will be described in terms of minimum and maximum, quartiles, means, and standard variations. Two-way repeated measures ANOVAs will be performed with the within-group factors of condition (a-tDCS/ c-tDCS/sham-tDCS) and moment (pre- and post-tDCS) for endurance performance or explosive performance. Bonferroni corrections will be employed to correct for type I errors due to multiple testing. The sphericity assumption will be tested using the Mauchly’s test and the Greenhouse-Geisser correction will be used whenever data sphericity is violated. The level of significance will be set at *p* ≤ 0.05. Subgroup analysis (level of practice) will be descriptive because of the small sample size of the study. Means and proportions will be calculated with their 95% confidence interval. All valid data will be used at different times of the study. There is no strategy for replacing missing data.

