To clarify the effect of tDCS on these different types of neuromuscular performance, we propose to evaluate the acute and repeated effects of tDCS during two tasks: an explosive task (jumps) and an endurance task (20-min cycling trial). The main objective is to compare the effects of tDCS applied over the left dlPFC with sham tDCS on the performance of the neuromuscular system. In the present protocol, the choice has been made to recruit participants with different backgrounds regarding sports practice, from sedentary people to high-level athletes in the targeted performance (parkour athletes for explosive performance or cyclists for endurance). Indeed, the tDCS effects on physical performance could also be a function of the initial level [23].

This study is a monocentre, sham-controlled, randomised, crossover, double-blinded superiority trial comparing active tDCS versus sham tDCS. It is divided into two parts: part A with the jumpers and part B with the cyclists. We hypothesise that the active tDCS sessions will improve motor performance and reduce neuromuscular fatigue. We will seek a better understanding of the factors that could cause tDCS effects to vary: stimulated brain area, exercise type (explosive vs enduring), tDCS configuration (cephalic vs extracephalic montage), and the number of tDCS sessions (single vs repeated stimulations).

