The BART task is a computer-based measure of the risk-taking [34]. During this task, the subjects must press a button to inflate a series of 30 balloons displayed on the computer. Each pump corresponds to 5 cents, which are accumulated in a temporary bank (the amount of which is unknown to the subject). At any time, the subjects can collect the money obtained in a definitive bank (the amount of which is displayed on the computer). However, if the balloon explodes before collection, the money accumulated in the temporary bank is lost and a new balloon appears on the screen. Each balloon has a different probability of explosion and the subject’s objective is to make as much money as possible. Risk-taking behaviour will be measured by the adjusted average number of pumps (only trials in which the balloons did not explode are included in the calculations).

The tDCS effects on motivation will be measured using the Effort Expenditure for Rewards Task (EEfRT) [35]. It is a computerised effort-based decision-making task. For each trial, the subject must choose between an easy and a difficult task.

During the easy task, the subject must press the “L” key on the keyboard with the index finger of the right hand and can earn 1€ according to the probability of retribution. During the hard task, the subject must press the “S” key with the pinkie of the left hand and can earn between 1.24 and 4.30€ (“reward magnitude”) according to the probability of retribution. The probability of reward retribution varies at each trial; an indication of this probability (12%, 50%, or 88%) is given before the choice. The subject thus makes a choice between easy and difficult tasks according to the probability of reward and the reward magnitude. Motivation is modelled by the percentage of hard task choices.

All of these tasks will be performed before and after each tDCS session (jumpers), or before and after the first and the last tDCS session, and at day 12 and day 30 of each sequence (cyclists).

A comparison of inter-condition scores and scores before and after tDCS session/sequence will be made.

Finally, depression severity will be assessed by the clinician (QIDS-C16) and self-reported by the subject (QIDS-SR16) [36].

The QIDS-SR16 has 16 items (score range from 0 to 27) assessing the severity of depressive symptoms as perceived by the subject, with the following cut-off points: 0–5 none; 6–10 mild; 11–15 moderate; 15–20 severe; and 21–27 very severe depression.

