### Outcomes

Our efficacy criteria will be the evaluation of neuromuscular performance during an explosive task (main outcome, part A) or during an endurance task (secondary outcomes, part B).

In part A, we will compare the height of the vertical jumps (in centimetres) or the length of horizontal jumps (in centimetres) performed before and after active or sham tDCS session. In part B, endurance performance will be assessed by comparing the average power output (in watts) during a time-trial realised before, after the first, on the last tDCS session, and at day 12 and day 30 of each sequence.

Secondary efficacy criteria include:

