### Sample size

Our sample size calculation is based on the primary efficacy outcome that relates to changes in motor performance before and after a tDCS session during an explosive task (jumps). In a previous study, Lattari et al. [22] showed an 11.2% improvement in the height of the CMJ following a tDCS session, corresponding to a difference of 3.9 cm (Table 1 of Lattari’s et al.). We expect a 15% improvement in our study corresponding to a difference of 5.1 cm. No difference is expected in the sham tDCS group. Considering a significance level of 5%, a power of 90%, and a standard deviation for paired differences of 6.5 (calculated from standard deviations, page 21, Table 1 with an hypothesis of a covariance of measures of 50%), 20 jumpers are included to meet the objectives of the study. Sample size calculation was performed on PASS 13 Power Analysis and Sample Size Software (2014) [39, 40] .

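### Part A's objective is active left dlPFC versus sham, but its efficacy criterion and sample size are written as before-after comparisons, and the ANOVA does not name the deciding contrast

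*Protocol article*

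**What the plan says.** Four sections of the protocol article bear on which comparison decides efficacy in part A.

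- **Background.** The main objective is to "compare the effects of tDCS applied over the left dlPFC with sham tDCS", and the trial is described as a sham-controlled superiority crossover.
- **Outcomes.** The part A criterion is jump height or length "performed before and after active or sham tDCS session". No difference between the two changes is mentioned.
- **Sample size.** The primary outcome is "changes in motor performance before and after a tDCS session during an explosive task (jumps". The anticipated gain is 5.1 cm, or 15%. For sham, the assumption reads "No difference is expected in the sham tDCS group". With two-figure inputs of 5% significance and 90% power, and 6.5 as the SD of the paired differences, the result is 20 jumpers.
- **Data management and statistical analyses.** "Two-way repeated measures ANOVAs will be performed with the within-group factors of condition (a-tDCS/ c-tDCS/sham-tDCS) and moment (pre- and post-tDCS". The significance level is 0.05 with Bonferroni correction. The interaction is not mentioned, and no effect is singled out.

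Two other places refer to both kinds of comparison without ranking them. The study overview adds that active and sham outcomes will be compared after unblinding. For the cognitive tasks, "A comparison of inter-condition scores and scores before and after tDCS session/sequence will be made".

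**The concern.** A condition-by-moment ANOVA yields three tests, and they answer different questions. The moment effect asks whether jumps after stimulation differ from jumps before it, averaged over active and sham sessions. The condition effect averages in the jumps made before stimulation, which that session's tDCS cannot have influenced. Only the interaction compares changes between conditions, and only its dlPFC-versus-sham component answers the stated objective.

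The Outcomes and Sample size sections describe something else: a change from before to after a session. Warm-up, practice or fatigue can move jump performance within a session whatever the stimulator delivers. The protocol makes such a shift plausible. In part A, jumps, maximal contractions and cognitive tasks are done before and again immediately after stimulation, and the long jump is repeated until it stops improving. In part B, ten submaximal cycling sessions lie between the pre- and post-sequence time trials under active and sham alike, and some participants are sedentary.

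If the before-after wording were followed, an improvement common to active and sham could be reported as an effect of tDCS. Bonferroni correction does not address this, because a shared shift is a real effect of time and not a chance finding.

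**Working it through.** **Inputs from the Sample size section.** Difference 5.1 cm, SD of paired differences 6.5 cm, significance level 5%, power 90%, sham change 0, n = 20. Sidedness is not stated.

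**1. Reproduce the stated n.** Paired t-test of one before-after change, two-sided 5%, noncentral t with noncentrality 5.1 × √n / 6.5.
- n = 19: power 0.898.
- n = 20: noncentrality 3.51, power 0.914.

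The smallest n reaching 90% is 20, as stated. A one-sided test would need 16. The stated figure is therefore what a two-sided test of a single before-after change requires.

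**2. Before-after test after dlPFC with no tDCS effect.** Assume a shift s common to every session. The protocol gives no size for it, so 1, 2 and 3 cm are assumptions. Noncentrality is s × √20 / 6.5.
- s = 1: 0.69, significant in 10% of trials.
- s = 2: 1.38, significant in 26%.
- s = 3: 2.06, significant in 50%.

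**3. Main effect of moment with no tDCS effect.** This tests the mean of a subject's three changes. With correlation ρ between changes in different sessions, its SD is 6.5 × √((1 + 2ρ)/3).
- ρ = 0: SD 3.75; significant in 20%, 62% and 92% for s = 1, 2 and 3.
- ρ = 0.5: SD 5.31; significant in 13%, 36% and 67%.

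**4. dlPFC-minus-sham change.** The shift cancels: (0 + s) − (0 + s) = 0. The false-positive rate is 5% for every s and ρ. In simulation of the three-condition design (20,000 runs per scenario), the overall interaction test likewise stayed between 0.046 and 0.053.

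**5. Power for the contrast that matches the objective.** The difference is 5.1 − 0 = 5.1 cm and the SD is 6.5 × √(2(1 − ρ)), where ρ is now the correlation between a subject's active and sham changes. The protocol does not give it, so a range is shown.

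| ρ (assumed) | SD (cm) | Power at n = 20 | n for 90% |
|---|---|---|---|
| 0 | 9.19 | 0.65 | 37 |
| 0.25 | 7.96 | 0.78 | 28 |
| 0.5 | 6.50 | 0.91 | 20 |
| 0.75 | 4.60 | 0.997 | 11 |

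**The case against.** The best defence is that the sham comparison is plainly intended. The objective names it, the overview repeats it, and the ANOVA carries sham as a level of condition; given that objective, the interaction is the natural effect to read. The Outcomes wording may simply describe how jumps are measured in each session. The sample size sets 5.1 cm beside a sham change of zero, so the implied active-minus-sham difference is also 5.1 cm, and n = 20 fits that contrast at a correlation of 0.5. Which effect of a stated ANOVA decides is also often left to an analysis plan, and none is shown here.

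Much of this stands: the design can answer the question, and silence about the deciding F test would not alone be a finding. What remains is a conflict in the printed text. The criterion and the stated basis of the sample size describe a before-after change while the objective describes a comparison with sham, and an analysis plan that named the interaction would still have to override those two sections. The word exploratory in the title does not settle it, because the protocol also calls itself a superiority trial and powers a primary outcome.

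A reader might infer more than the documents support:
- That a before-after gain under active stimulation is the declared success rule. No section says so.
- That significance after active but not after sham would count as efficacy. That rule appears nowhere.
- That any one of the three F tests would count. This is not stated either, and the planned Bonferroni correction could cover that multiplicity.

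**Conclusion.** The point holds as an inconsistency to be resolved. The objective calls for a contrast of changes between active left dlPFC and sham; the efficacy criterion and the sample size are phrased as before-after; the planned model contains the right test without naming it.

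The exposure is 10% to 50% false positives for the before-after test, and 13% to 92% for the moment effect, over assumed shared shifts of 1 to 3 cm. The moment figures also depend on how strongly changes correlate across sessions. The contrast that uses the sham control stays at 5%. These rates show what the before-after wording would permit; they do not predict what the trial will report.

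It would also go too far to call the trial underpowered for the correct contrast. At a correlation of 0.5 or more, 20 jumpers meet the 90% target; at 0.25 or less they do not, and the protocol gives no value.

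**What to change.** In the Outcomes and statistical analysis sections, state that the deciding part A test is (post minus pre under active left dlPFC) minus (post minus pre under sham), two-sided at 5%, and that the condition and moment main effects and the within-condition before-after tests are descriptive only. Define the contrast by stimulation site, since the condition labels in the ANOVA sentence do not identify the dlPFC session.

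Restate the Sample size section on the same contrast, giving the assumed correlation between a subject's active and sham changes and the resulting SD and power.

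For part B, which is secondary, use the active-minus-sham change at one named post-sequence time point. Several follow-up assessments are planned, so post minus pre is not a single contrast there.

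This needs no new data. The cost is that a before-after improvement alone can no longer be claimed as efficacy, and the stated 90% power becomes conditional on the correlation.

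### The condition-by-moment ANOVA compares active with sham tDCS on change scores; adjusting for the same-session pre-tDCS value would be more precise, by an amount that depends on a correlation the protocol does not give

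*Protocol article*

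**What the plan says.** The Background gives the main objective as to "compare the effects of tDCS applied over the left dlPFC with sham tDCS on the performance of the neuromuscular system". Under Outcomes, part A compares jump heights or lengths "performed before and after active or sham tDCS session", so every condition has its own pre-tDCS value from the same visit.

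The only inferential model named for performance is in the section on data management and statistical analyses: "Two-way repeated measures ANOVAs will be performed with the within-group factors of condition (a-tDCS/ c-tDCS/sham-tDCS) and moment (pre- and post-tDCS"), for explosive or endurance performance, with Bonferroni correction for an unstated number of tests. The pre value enters as a level of the response. No baseline covariate is named.

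The Sample size section supplies the figures: "We expect a 15% improvement in our study corresponding to a difference of 5.1 cm", "No difference is expected in the sham tDCS group", and "Considering a significance level of 5%, a power of 90%, and a standard deviation for paired differences of 6.5". The last of these is "calculated from standard deviations, page 21, Table 1 with an hypothesis of a covariance of measures of 50" per cent. The result is 20 jumpers.

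**The concern.** When a response has two moments, the interaction of condition and moment, taken for active versus sham, is the paired test of (post minus pre under active) minus (post minus pre under sham). Equivalently, it is the active-minus-sham difference in post values, minus 1 times the same difference in pre values.

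In a parallel-group trial that subtraction removes much of the variation between subjects. In a crossover that variation has already gone, because each subject is compared with himself or herself. What is left in the pre difference is mostly visit-to-visit noise. Subtracting all of it helps only when it tracks the post difference closely. Estimating the coefficient from the data keeps whatever information the pre value holds and adds less noise.

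What is at stake is precision on the main contrast with 20 subjects, using measurements the trial already plans to take. Bias is not in question.

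**Working it through.** **Inputs from the Sample size section.** Effect 5.1 cm under active and 0 under sham, so the contrast is 5.1 cm; SD of pre-post differences 6.5 cm; n = 20; alpha 5%, taken as two-sided. The 50% covariance is read as a pre-post correlation of 0.5, so the single-measure SD is 6.5/√(2 × (1 − 0.5)) = 6.5 cm.

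**Assumption not in the documents.** The between-session correlation ρ_b of a subject's jumps at different visits. It is varied from 0 to 0.5, that is, up to the within-session value.

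**Step 1: the plan's own figure.** A paired t-test (noncentral t) with difference 5.1 and SD 6.5 has 89.8% power at n = 19 and 91.4% at n = 20. The stated 20 for 90% reproduces. It is the size for a pre-post change within one condition.

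**Step 2: active versus sham under the planned model.** The variance of the difference between two changes is 4 × 6.5² × (1 − 0.5) = 84.5, so the SD is 9.19 cm whatever ρ_b is. Power at n = 20 is 65.3% on 19 df. With error pooled over three conditions (38 df, sphericity assumed) it is 67.7%. The omnibus interaction has 69%, whether the second active condition has an effect of 0 or 5.1 cm.

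**Step 3: baseline-adjusted contrast.** For two conditions with subject fixed and no period term, this is the regression of the post difference on the pre difference, testing the intercept. The correlation between those differences is r = (0.5 − ρ_b)/(1 − ρ_b). The adjusted variance is 2 × 6.5² × (1 − ρ_b) × (1 − r²), which is (1 + r)/2 times the change-score variance. Power uses 18 df and inflates the variance by 1 + 1/17 for the estimated slope.

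| ρ_b (assumed) | r | variance ratio | planned power | adjusted power | gain |
|---|---|---|---|---|---|
| 0 | 0.50 | 0.75 | 65% | 75.0% | 10 points |
| 0.3 | 0.29 | 0.64 | 65% | 81.2% | 16 points |
| 0.5 | 0 | 0.50 | 65% | 89.7% | 24 points |

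Simulated trials of 20 subjects agree: about 75%, 81% and 90% adjusted against 65% planned, with type I error of the adjusted test near 5%.

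**Step 4: where the gain shrinks.**

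- *SD of the change contrast kept at 9.19 cm, r raised.* Adjusted power is 68% at r = 0.75, 67% at r = 0.8 and 65% at r = 0.9, so the gain is about 3, 2 and 0 points.
- *Single-measure SD kept at 6.5 cm, correlations raised (within/between session).* Planned versus adjusted power is 86% vs 94% at 0.7/0.5, 86% vs 91% at 0.7/0.3, 96% vs 99% at 0.8/0.7, and about 100% for both at 0.9/0.8. The gain is 0 to 8 points.

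**Step 5: Bonferroni.** The figures above are before correction. At 0.025 or 0.0167, planned power for the two-condition contrast falls to 53% or 46%.

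**The case against.** The strongest reply is that nothing here is wrong. The ANOVA is unbiased, it matches an outcome defined as change around a session, and the title calls the trial exploratory. The article neither labels the ANOVA primary nor names the interaction as the test. All of this stands. Still, it is the only inferential model given, and the interaction is the term that compares change between conditions. The point concerns a stated choice that can be improved at almost no cost.

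The second reply is that the size is not fixed by the plan. This also stands. A reader might infer that the 10 to 24 points follow from the plan's inputs alone. They do not: ρ_b is an assumption, and both ends are extreme. Zero means that one athlete's jumps at two visits are unrelated; 0.5 means that separate visits agree as well as pre and post on the same day. The pre-post correlation of 0.5 is itself only a planning hypothesis. If 6.5 cm were already the SD of the active-minus-sham contrast, planned power would be 91% and the gain about 5 to 8 points for r between 0 and 0.5. But the Sample size section ties that SD to change before and after a session and deals with sham separately, so the pre-post reading is the natural one.

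A reader might also attribute the whole drop from the stated 90% to 65% to the model. It arises because the trial was sized on a change within one condition. That is a separate issue and is not claimed here, although adjustment happens to win back part of it.

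Nor can a loss be put on part B: no effect, SD or correlation for time-trial power is given, and endurance is a secondary outcome.

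Finally, the absence of athletic level from the model is no part of this point. It is constant within subject and cancels from the contrast.

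**Conclusion.** The point holds as one of efficiency. The planned active-versus-sham comparison fixes the baseline coefficient at 1 where a crossover gives little reason to.

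On the Sample size figures, and with an assumed between-session correlation of 0 to 0.5, baseline adjustment raises power from about 65% to between 75% and 90%. That is a gain of roughly 10 to 24 points, or 2 to 4 points less measured against the pooled-error three-condition ANOVA. The gain is about 0 to 8 points if the pre-post correlation is well above 0.5 at the same single-measure SD, and close to nil if the pre and post differences are very highly correlated. Results from the planned ANOVA would remain valid. The change is worth making because it is cheap and the sample is small.

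**What to change.** In the section on data management and statistical analyses, make the active-versus-sham analysis of each jump outcome a baseline-adjusted crossover model:

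- outcome: the post-tDCS value;
- fixed effects: condition, period (visit) and subject;
- covariate: the pre-tDCS value from the same session.

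If subject is random, enter the pre value as its subject mean plus its within-subject deviation, so that differences between subjects do not drive the slope. Keep the condition-by-moment ANOVA as a supportive analysis. The same form can be used in part B, with pre-sequence mean power as the covariate for each post-sequence time.

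The cost is a wording change, a standard SAS mixed model, a few degrees of freedom and the assumption of a linear baseline effect. No further subject or measurement is needed. The model should be fixed before unblinding, since a covariate chosen afterwards would be open to challenge.

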## Methods/design

### Study setting and overview

This research will be carried out through a collaboration between the Psychiatric Department of the University Hospital of Besançon and the scientists from the Faculty of Sports of the University of Besançon (C3S Laboratory). All experiments will take place on the EPSI research platform (Entraînement Performance Santé Innovation, Besançon, France). This protocol will be divided into two parts to explore the effects of tDCS by type of exercise:
Part A, which assesses the effects on explosive performance (jumps)Part B, which assesses the effects on endurance performance (cycling time trial)

Fifty subjects (20 in part A, 30 in part B) will be recruited from the university or from federated organisations of sports. For part A, athletes practicing parkour, an activity that consists of jumping obstacles in various environments, have been chosen since they usually present a very explosive neuromuscular profile [24]. For part B, amateur and professional cyclists will be recruited. After information about the study, written informed consent will be obtained.

In part A, subjects will be divided into two groups (amateur vs high-level practice) and receive three sessions of tDCS (active over the left dlPFC vs active over the right M1 vs sham over the left dlPFC). The session order will be randomised (Fig. 1).

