**Fig. 2 Fig2:**
[figure not shown]
Study flow diagram (part B)

Common measurements for parts A and B will include: clinical assessment of impulsivity based on self-report scales and behavioural tasks, task-based measures of motivation, and assessment of neuromuscular function—electromyographic (EMG) recordings and evoked potentials from nerve percutaneous stimulation. These measures will be taken before and after each brain stimulation session (part A) or before and after each brain stimulation sequence, and at day 12 and day 30 (part B).

For each group, baseline measures will include a clinical assessment of depression severity, based on the Quick Inventory Depression Scale-Clinician version (QIDS-C16) and on the self-reported version (QIDS-SR16). These data will be compared to those obtained after the last tDCS session and at days 12 and 30 (part B).

In order to assess the tDCS effects on two types of physical performance, the physical tasks will differ between parts A and B. In part A, the performances assessed will be jumping tasks—squat jump (SJ), countermovement jump (CMJ), and standing long jump (SLJ)— while in part B, an endurance task (20 min cycling time trial) will be performed. The endurance task will be performed maximally pre- and post-tDCS sequence, then at day 12 and day 30, while it will be performed sub-maximally (60% of peak power) during each online tDCS training session (i.e., twice a day for 5 days). In part B, other measures will be performed at the start, immediately after the last session of tDCS and then at day 12 and day 30 (see “Study procedure” section for details). After unblinding, active and sham stimulation outcomes will also be compared.

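### Both crossovers are analysed by an ANOVA with no period term, and its need for complete data is hard to square with using all valid data

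*Protocol article*

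**What the plan says.** The only inferential model is in Data management and statistical analyses: "Two-way repeated measures ANOVAs will be performed with the within-group factors of condition" and moment, where moment has the levels pre- and post-tDCS. Both factors of the two-way model are named, and neither is period. Sequence, order and carry-over are not mentioned in that section. Sphericity is to be tested by Mauchly's test, and the "Greenhouse-Geisser correction will be used whenever data sphericity is violated". On incomplete data the same section says "All valid data will be used at different times of the study. There is no strategy for replacing missing data". Under Withdrawal of consent the protocol adds: "Withdrawals of consent will be replaced".

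The design is a three-session crossover in part A (20 jumpers, at least 48 h between sessions) and a two-sequence crossover in part B (30 cyclists and sedentary subjects, one month of wash-out). For part A, Study setting and overview states "The session order will be randomised" and gives no balancing rule. For part B it says that the endurance task is ridden sub-maximally "during each online tDCS training session (i.e., twice a day for 5 days", between the maximal trial before each sequence and the one after it.

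**The concern.** In a crossover each participant is compared with himself or herself at another time, so anything that changes with time competes with treatment. Wash-outs guard against carry-over of stimulation. They do not guard against practice, training or tiring.

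Because moment is in the model, the treatment effect is the condition-by-moment interaction, that is, the difference between conditions in pre-to-post change. The relevant threat is therefore a change that differs by period. Part B builds in a candidate: ten rides fall between the pre and post trials of each sequence, some riders are sedentary, and a larger training gain in the first sequence than in the second would be unsurprising. In part A the jumps and cognitive tests are done six times, so a diminishing practice gain is possible.

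The second issue is incomplete data. A repeated measures ANOVA with Mauchly's test and the Greenhouse-Geisser correction works on one complete vector per participant. With nothing replaced, a jumper who lacks only the motor-cortex visit leaves the analysis even though the dlPFC and sham visits are complete. The sample size has little room for such losses.

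**Working it through.** **1. The plan's own figure.** Inputs from Sample size: difference 5.1 cm, SD of paired differences 6.5 cm, level 5%, power 90%. A two-sided paired t-test (noncentral t) gives n = 20 with power 0.914, so the stated number reproduces. Power is 0.898 with 19 complete participants, 0.880 with 18, 0.859 with 17 and 0.807 with 15.

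**2. What an omitted period effect does.** Let π be the period difference in pre-to-post change (earlier minus later), δ the true active-sham difference in change, n1 the number with active first and n2 the number with sham first. A participant's active-minus-sham difference has mean δ + π with active first and δ − π with sham first. Without a period term the estimate averages

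δ + π × (n1 − n2) / (n1 + n2).

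- 10:10 split: bias 0.
- 12:8 split: bias 0.2π, which is 0.5 cm for π = 2.5 and 1.0 cm for π = 5.1.
- 14:6 split: bias 0.4π, which is 1.0 cm for π = 2.5 and 2.0 cm for π = 5.1.

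At 10:10 the period effect enters the error instead. The expected variance is 6.5² + π² × 20/19:

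- π = 2.5: 42.25 + 6.58 = 48.83, SD 6.99.
- π = 5.1: 42.25 + 27.38 = 69.63, SD 8.34.

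A simulation of this two-period model (n = 20, 40,000 runs per case, 6.5 taken as the SD of the active-minus-sham difference) gave, at 10:10:

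| π (cm) | Power without period | Power with period | Type I error without period |
|---|---|---|---|
| 2.5 | 0.887 | 0.912 | 0.037 |
| 5.1 | 0.786 | 0.913 | 0.015 |

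At 12:8 with the period term, bias is about 0 and power about 0.90. The values of π are assumptions; 5.1 cm equals the whole expected treatment effect and is an extreme case. Part A has three periods, so the two-period model is a simplification there. Part B's outcome is in watts with no SD stated, so only the multiplier of π carries over.

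**3. How likely imbalance is.** If order in part A were unrestricted (an assumption), the number of jumpers with dlPFC before sham would be Binomial(20, 0.5). P(6 or fewer, or 14 or more) = 2 × 60,460 / 1,048,576 = 0.115. Exact balance over the six possible orders is impossible in any case, since 20 is not a multiple of 6.

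**4. Loss from needing complete vectors.** The documents give no missing rate. With rate m per unit, k units per participant and independence, the share lost is 1 − (1 − m)^k.

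| Case | k | m = 5% | m = 2% |
|---|---|---|---|
| Part A, whole visits missed | 3 | 14.3% | 5.9% |
| Part A, six cells missing independently | 6 | 26.5% | 11.4% |
| Part B, two conditions × pre/post | 4 | 18.5% | 7.8% |

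At 5% this leaves about 17.1 or 14.7 of 20 jumpers (power about 0.86 or 0.81) and 24.4 of 30 in part B. At 2% it leaves about 18.8 or 17.7 jumpers (power about 0.90 or 0.88) and 27.7 in part B.

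**The case against.** The strongest defence is that most learning, training and fatigue does no harm here. Outcomes are compared before and after each session, so any shift that moves both values of a period equally drops out of the tested interaction. That is correct, and it limits the concern to period differences in the change. A reader might infer that all learning or fatigue across visits ends up in the treatment estimate; the stated model does not support that.

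The protocol also limits such effects. It has a habituation session, a standardised warm-up, several trials per jump, a long jump repeated until it stops improving, and a one-month gap in part B. These make a large π less likely but do not exclude it, least of all for the training response in part B.

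Unrestricted order is not stated. Recruitment and randomisation describes minimisation stratified by athletic level and a control subject sharing the same randomisation sequence. The wording is unclear and does not say that sequence order is balanced, but it prevents treating 11.5% as the trial's own risk.

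On missing data, no SAS procedure is named and case deletion is not written out. The phrase about valid data may mean whatever is available at each time point. That reading suits the descriptive statistics; the stated ANOVA still cannot use a partial vector.

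Two stronger readings go too far. First, one might conclude that the analysis is of completers only and selects those who tolerated every session. The protocol says withdrawals are replaced, not that their data are discarded. Second, counting all four part B time points per sequence gives eight cells and a 34% loss at 5% missing. Moment is defined as pre and post only, so a missed day 12 or day 30 visit would not remove anyone from this ANOVA.

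**Conclusion.** The point holds in this limited form. The protocol fixes a model without period for two randomised crossovers, and this is a stated method rather than detail left to an analysis plan. The harm depends on a period difference in the pre-to-post change, which is plausible in part B and possible in part A. With unbalanced orders it biases the contrast by the imbalance times that difference (0.4 times at 14:6). With balanced orders it costs precision and makes the test conservative: power falls from 0.91 to 0.89 for a 2.5 cm difference, and to 0.79 in the extreme 5.1 cm case.

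The complete-vector requirement is inferred from the method, and it is hard to reconcile with the promise to use all valid data. Its size rests wholly on assumed missing rates: 14% to 26% of jumpers and about 19% of cyclists at 5%, and 6% to 11% and 8% at 2%. The documents do not show that bias will occur or that withdrawn participants' data will be thrown away. The trial is labelled exploratory and part B performance is a secondary outcome. The change is still worth making because it is cheap and settles both issues.

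**What to change.** Replace the ANOVA by a linear mixed model fitted by REML, with participant as a random effect, using every observed session. Include the sessions of participants who withdrew and were replaced, where their consent allows use of data already collected. Period must be able to act on the change, so choose one of two forms:

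- Keep condition, moment and condition-by-moment, and add period and period-by-moment.
- Model the post value (or the change) with condition, period and that period's own pre value.

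A period main effect alone in the first form would not solve the problem, because it removes only the level shift that already cancels. Sequence and practice level may be added as between-subject terms. State how incomplete participants are handled, so that the sentence on valid data matches the method. While that text is open, align the listed condition levels (a-tDCS, c-tDCS, sham) with the conditions given in each part: dlPFC, motor cortex and sham in part A; active and sham in part B.

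Cost: one (part B) or two (part A) within-subject degrees of freedom for period acting on the change; up to five between-subject degrees of freedom if all six part A orders are fitted as sequence; a few lines of text and SAS code. No new data are needed.
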